# Analysis

Primary quantitative analysis will be by Intention to Treat (i.e. as planned) and modified Intention to Treat (i.e. as delivered). Exploratory analysis will assess the influence and associations of explanatory and potentially confounding variables. The findings will help determine whether randomization for subsequent trials needs to be simple or stratified.

Subgroup analysis will be employed, where possible with the number of patients in each group, to detect clinically important differences between subgroups that may be defined by age, gender, ethnicity, rural-urban dwelling and severity of initial health assessments.

There will be no imputation of missing data. All analyses will be conducted in Stata. Continuous variables will be analysed using mixed effects models that included site as a fixed effect, patient as a random effect and adjusted for age and gender. The main outcome for the psychometric scales will be assessed from the interaction between intervention group and time. Negative binomial regressions will be used to model count data including numbers of hospital attendance, length of stay and costs in analyses were adjusted for patient age, gender, ethnicity, and site as a factor variable. Exposure, for hospital use, will be measured by days alive and not in hospital. Exposure, for total days in hospital, will be measured by days alive. Results will be considered statistically significant when p ≤ 0.05.

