# Eligibility

**Inclusion criteria:**

1. *All areas*
   1. age 16+
   2. living permanently at home
   3. expected to be available for 3 months
   4. expected to survive study period
   5. able to communicate in English (or someone in household able to translate)
   6. able to physically manage the equipment (or someone available to assist)
2. A*uckland* – Permanently resides in the Auckland DHB region, current or recent in-patient to Auckland City Hospital with heart failure as the primary reason for admission
3. *Counties Manukau* – Permanently resides in the Counties Manukau DHB region, enrolled with ProCare PHO, current or recent in-patient at Middlemore Hospital with COPD as the primary reason for admission
4. *Tairawhiti* – Permanently resides in the Tolaga Bay area, enrolled with Ngati Porou Hauora PHO, and is on the PHO chronic condition management programme
5. *Canterbury* – Permanently resides in the Canterbury DHB region, enrolled with practices working with the community specialist respiratory service, with COPD being treated with Long Term Oxygen Therapy (LTOT) at home

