# Statistical Issues

**Potential patients available and recruitment rate**

We estimate that about two thirds of those invited to participate will consent, about 20% will drop out. In addition, for COPD and heart failure, we estimate that the death rate will be about 20% per year.

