**Sample size**

Each region will be a stand-alone and discrete trial though with some shared outcomes. Standard criteria and measures will apply across all trials. A sample size of 120 within Auckland, Counties Manukau and Canterbury will provide a power of 90% with alpha = 0.05 to detect a 10 point increase in SF36. Similarly, the literature (Bourbeau) suggests we need 86 patients in each study arm to have 90% power (alpha 0.05) to detect a mean change of 4 (the minimum important difference) on the St George Respiratory Questionnaire. Detecting some other outcomes will require more patients.

See separate document, “ASSET planning and power calculations” for details of data underlying power calculations.

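### Two analyses are both primary, one of them an undefined as-delivered analysis that departs from the randomised groups, and nothing says which governs if they differ

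*Protocol*

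**What the plan says.** The Analysis section of the protocol reads: "Primary quantitative analysis will be by Intention to Treat (i.e. as planned) and modified Intention to Treat (i.e. as delivered". Intention to treat comes first, but the two are joined as one primary analysis. The second is not called secondary or a sensitivity analysis. The section does not say what counts as delivered, what happens to telecare patients who fall short of it, or which result decides if the two disagree. One criterion covers everything: "Results will be considered statistically significant when p ≤ 0.05".

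Under Randomisation and study group assignment, individuals are randomised in Auckland and Counties Manukau, directly after baseline data collection. In Canterbury, general practices are randomised. Receipt and use of the equipment therefore come after assignment at all three sites.

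Under Terminology in the Background, the study is described as a source of pilot data, including on effect size, for planning later trials, and as underpowered for most outcomes. The Sample size section nevertheless sets an inferential target: 120 patients "will provide a power of 90% with alpha = 0.05 to detect a 10 point increase in SF36".

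**The concern.** A modified intention-to-treat set normally keeps patients in their assigned arm and makes a few stated exclusions. Grouping or selecting patients by what they received is a different analysis. If undelivered patients are counted with the comparator, it is as-treated. If they are left out, it is of per-protocol type, and the exclusion falls on the telecare arm alone, because controls have no equipment to fail to receive. Either way, the groups compared are no longer the groups that randomisation made alike.

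Two things are at stake. First, a selection-prone estimate has primary status, and with no precedence rule a discordant pair of results has no settled interpretation. Second, the study exists partly to supply an effect size for the follow-up trial. An estimate inflated by selection would make that trial too small.

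**Working it through.** **No printed figure is in dispute.** The protocol gives no rate of non-use and no link between non-use and prognosis. Both are assumed below and varied.

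**Admissions, no true effect.** Let *f* be the share of the telecare arm that does not use the equipment, and *k* the admission rate of these patients relative to users (users = 1). Randomisation gives the control arm the same mix. With equal arms the arm size cancels.

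- Expected rate in each randomised arm: 1 − f + fk. The intention-to-treat ratio has expectation 1.00.
- Telecare group as delivered: users only, rate 1.
- Non-users moved: comparator rate = [(1 − f + fk) + fk] / (1 + f), so RR = (1 + f) / (1 − f + 2fk).
- Non-users dropped: comparator rate = 1 − f + fk, so RR = 1 / (1 − f + fk).

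| f | k | RR if moved | RR if dropped |
|---|---|---|---|
| 0.10 | 1.5 | 1.10/1.20 = 0.92 | 1/1.05 = 0.95 |
| 0.15 | 2 | 1.15/1.45 = 0.79 | 1/1.15 = 0.87 |
| 0.20 | 3 | 1.20/2.00 = 0.60 | 1/1.40 = 0.71 |

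The middle row is a spurious reduction of 21% (moved) or 13% (dropped).

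**Direction.** At k = 1 both formulas give exactly 1. For k > 1 both fall below 1, and for k < 1 both rise above 1. The sign of the bias depends entirely on whether non-users are sicker or healthier.

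**Continuous outcome, no true effect.** The protocol prints no standard deviation for the SF-36, so one was back-solved. This takes 120 as a site total (60 per arm), two-sided alpha 0.05 and 90% power: SD = 10 / [(1.960 + 1.282) × √(2/60)] = 16.9. In 6,000 simulated trials per scenario, 20% of the telecare arm was undelivered. Non-delivery was unrelated, moderately related or strongly related to a poorer outcome (0, 0.5 or 1.0 log-weight per SD).

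| Link to outcome | Spurious benefit, moved / dropped (points) | Type I error of as-delivered test, moved / dropped | Trials where the two analyses disagree on significance, moved / dropped |
|---|---|---|---|
| none | 0 / 0 | about 5% to 6% | 6% / 3% |
| moderate | 3.0 / 1.8 | 17% / 9% | 17% / 8% |
| strong | 5.5 / 3.3 | 44% / 19% | 44% / 19% |

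Intention to treat stayed at 4.8-5.8% over all scenarios run, near the nominal 5% given a simulation standard error of √(0.05 × 0.95/6000) = 0.3 percentage points.

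The simulation is simple. It ignores clustering in Canterbury, and it ties non-delivery directly to the outcome. The protocol's scale analysis tests the group-by-time interaction, so the simulated outcome is best read as change. A stable baseline difference between users and non-users would largely cancel. The admissions model has no such safeguard: its listed covariates are age, gender, ethnicity and site, none of which measures severity.

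**Two primary tests.** If either result may count, the chance of at least one false positive is 6.4-8.8% even when non-delivery is unrelated to outcome (10-30% undelivered). The bound for two independent tests is 1 − 0.95² = 9.75%. At 20% undelivered with a moderate or strong link, it is about 20-47% (moved) or 11-21% (dropped).

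**The case against.** **The analysis set may be defined in a statistical analysis plan.** That plan is not shown, and such definitions often sit there. This answers the missing definition, but not the point. The protocol itself gives the as-delivered analysis primary status, and a later plan would have to contradict that sentence to change it.

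**The milder reading is open.** A reader might infer that as delivered must mean reclassifying non-users as controls. The text does not say so. Leaving them out fits the modified intention-to-treat label at least as well, and the smaller figures then apply. The bias is reduced, not removed.

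**The bias need not favour telecare.** A reader might infer that it must, because the frailest patients would be the ones not to use the equipment. Nothing in the protocol links non-use to severity. Entry requires patients to be "able to physically manage the equipment (or someone available to assist", and the exclusion criteria cover significant cognitive impairment and serious current illness, which screens out some of the patients this mechanism needs. Nor do the planning statements that "about 20% will drop out" and "we estimate that the death rate will be about 20% per year" supply a non-use rate. They concern loss from the study and death.

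**Error inflation is conditional.** A reader might infer that the false-positive rate is inflated as the plan stands. The text does not say whether one significant result suffices or both are needed. Requiring both would not inflate it through multiplicity. That the better result would be reported alone is conjecture, since both analyses are pre-specified.

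**This is a pilot.** That lowers the stakes. But the effect estimate is itself one of the pilot's intended products, and the protocol still sets a power target and a significance threshold.

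**Conclusion.** The point holds in conditional form. The protocol fixes two primary analyses without precedence. One of them departs from the randomised groups on either available reading.

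The size of any bias is unknown. It is zero if non-use is unrelated to outcome, favours telecare if non-users are sicker, and goes against telecare if they are healthier. Under the assumed range with sicker non-users, a null effect on admissions would appear as a rate ratio of 0.92 to 0.60 if non-users are moved, or 0.95 to 0.71 if they are dropped. These figures show what the wording permits and do not predict what the trial will find. The documents do not support saying that the as-delivered result will favour telecare, or that type I error is inflated as written.

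**What to change.** In the Analysis section of the protocol:

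1. Make intention to treat by assigned arm (the practice's arm in Canterbury), using all available data, the sole primary analysis. State that it governs the conclusion and supplies the effect size carried to the follow-up trial.
2. Define delivered: what receipt or duration of use counts, and whether patients who fall short are moved or excluded. Study Design limits a loan to three months, while the Appendix 8 table for Canterbury plans six months per patient. These passages must be reconciled before a definition can refer to duration.
3. Rename the as-delivered analysis as-treated or per-protocol, according to that definition, and make it secondary or exploratory.

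This needs no extra patients or data. The cost is a few sentences and the loss of primary status for one analysis.

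If an effect of actually receiving telecare is wanted, a complier-average causal effect estimate is an option, but more than a change of wording. It needs a definition of receipt, an exclusion restriction and allowance for clustering in Canterbury. It would also be imprecise with 48 (Appendix 8) to 60 (half of 120) patients per arm.

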# Randomisation and study group assignment

Immediately after baseline data collection, participants in Auckland and Counties Manukau will be randomised to intervention or control arms. The researcher will phone an Interactive Voice Response (IVR) system via an 0800 number, provide basic patient identification data and be assigned a study group for that patient.**

*Eligible  consent  baseline data collection  individual randomly assigned to intervention or control*

In Christchurch, a pre-assigned cluster randomisation will assign participating general practice surgeries – and the patients attending them – to intervention or control arms of the study.

*Eligible  consent  baseline data collection  cluster randomised to intervention or control, based on randomly assigned group of patient’s general practice*

In Tairawhiti, patients will not be assigned to separate groups.

*Eligible  consent  baseline data collection  followed in telecare programme*

Note: initially we intended to randomise with stratification by age / gender / distance from hospital / ethnicity. We have decided against this as i) we are collecting pilot data and will find if we obtain an adequate stratification by including all who are eligible and consent ii) there are technical and efficiency reasons not to stratify. From this pilot data we will be better informed as to whether stratification will be necessary in a follow up trial.

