**Data and document handling**

The following table outlines the flow of information from recruitment to assessment.

Table 1: summary of data and document handling

| **Record** | **Data handling procedure** |  |
| --- | --- | --- |
| Eligible clients list | Stored electronically by local researcher; emailed to Study Manager weekly |  |
| Ineligible clients list | Stored electronically by local researcher; emailed to Study Manager weekly |  |
| Contact list | Stored electronically by local researcher; emailed to Study Manager weekly |  |
| Declined clients list | Stored electronically by local researcher; emailed to Study Manager weekly |  |
| Delayed Interview list | Stored electronically by local researcher; emailed to Study Manager weekly |  |
| Randomisation list | Auckland and Counties Manukau: researcher phones randomization service while still with patient, records on Care Report Form, updates local list of Intervention and Control patients, emails Study Manager within 24 hours.  Canterbury: researcher confirms general practice of patient, confirms and records Intervention or Control group, emails Study Manager within 24 hours. |  |
| Enrolled participant list | Local researcher maintains up-to-date list; emails to Study Manager weekly |  |
| Participant contact card | Local researcher maintains up-to-date list; emails to Study Manager weekly |  |
| Withdrawn participant list | Local researcher maintains up-to-date list; emails to Study Manager weekly |  |
| Participant research interview (CRF = Case Report Form) | Local researcher keeps original, faxes or emails Study Manager weekly. Transfers originals to Study Manager at end of study. |  |
| Interview recordings | Digital recording and field notes sent to Study Manager within 24 hours. |  |

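### Canterbury randomises general practices, but the stated models have no practice term and its 120 patients and 90% power match the individually randomised regions

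*Protocol*

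**What the plan says.** **Randomisation.** The protocol's section on randomisation and study group assignment uses two units. Individually, "participants in Auckland and Counties Manukau will be randomised to intervention or control arms". For the Canterbury trial, "In Christchurch, a pre-assigned cluster randomisation will assign participating general practice surgeries", and patients take the arm of the practice they attend. The table under Data and document handling confirms this: "Canterbury: researcher confirms general practice of patient, confirms and records Intervention or Control group".

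**Sample size.** "A sample size of 120 within Auckland, Counties Manukau and Canterbury will provide a power of 90% with alpha = 0.05", in order "to detect a 10 point increase in SF36". One figure serves all three regions. The section gives no SD, ICC, number of practices or patients per practice, and refers to a separate planning document for the underlying data.

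**Analysis.** Continuous outcomes get "mixed effects models that included site as a fixed effect, patient as a random effect and adjusted for age and gender"; the psychometric scales are judged by the interaction of group and time. Hospital attendance, length of stay and costs get negative binomial regression adjusted for age, gender, ethnicity and site. Neither model has a practice effect or cluster-robust standard errors. Significance is declared at p ≤ 0.05.

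**Meaning of site.** The Background section lists the four sites as the regions Auckland, Counties Manukau, Tairawhiti and Canterbury. Study Design and Sample size both describe each region as a discrete trial that stands alone.

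**The concern.** When practices are randomised, patients of one practice share an arm and may also share clinicians, habits of referral and admission, and local circumstances. If their outcomes are correlated, the difference between arms varies more than an analysis of independent patients assumes. Neither term in the stated models captures this. The patient effect handles repeated measurements on one person, and site is constant within Canterbury.

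Two things are at stake. Canterbury's p-values and confidence intervals could be too favourable, most clearly for hospital use and costs, which include primary outcomes. Its stated 90% power could also be too high. Both matter for a study whose declared purpose is to supply data for sizing later trials.

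**Working it through.** **Inputs from the protocol.** 120 patients per region, 90% power, alpha 0.05 (taken as two-sided), a 10-point SF-36 difference, practices randomised in Canterbury.

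**Inputs that must be assumed.** Patients per practice (m) and ICC. For the scales, the ICC is that of change, not of level.

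**1. The plan's own figure.** No SD is stated, so 120 can be neither confirmed nor refuted. Solving backwards with a normal approximation, where n is patients per arm:

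SD = 10 / [(1.960 + 1.282) × √(2/n)]

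- 120 in total (n = 60): SD = 16.9.
- 120 per arm (n = 120): SD = 23.9.

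Both values are back-solved, not protocol figures. Under either reading, 120 fits a design effect of 1. The same number gives the same power in all three regions only if the Canterbury ICC is 0, each practice supplies one patient, or the SDs differ.

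**2. Formulas under clustering.**

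- Design effect: DE = 1 + (m − 1) × ICC
- True type I error of the unadjusted 5% test: 2 × [1 − Φ(1.96/√DE)]
- Power when analysed correctly, starting from 90%: Φ(3.242/√DE − 1.960)

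The SD drops out of the power formula. Any SD that gives 90% without clustering makes the ratio of effect to standard error 1.960 + 1.282 = 3.242, so the two readings of 120 give the same loss.

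**3. Results for a stand-alone Canterbury comparison (m and ICC assumed).**

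| Patients per practice | ICC | DE | True type I error | Power at 120 |
|---|---|---|---|---|
| 1 | any | 1.00 | 5.0% | 90% |
| 2 | 0.01 | 1.01 | 5.1% | 89.7% |
| 3 | 0.05 | 1.10 | 6.2% | 87.1% |
| 8 | 0.05 | 1.35 | 9.2% | 79.7% |
| 12 | 0.10 | 2.10 | 17.6% | 60.9% |

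For the fourth row: DE = 1 + 7 × 0.05 = 1.35 and √1.35 = 1.162. Then 1.96/1.162 = 1.687, which gives 9.2%, and 3.242/1.162 − 1.960 = 0.83, which gives 79.7%.

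Simulating 120 patients in equal practices, analysed with an ordinary t-test, agrees with the formula: 7.5% against 7.4% (m = 5, ICC 0.05), 10.7% against 10.4% (m = 10, ICC 0.05), and 15.6% against 15.5% (m = 10, ICC 0.10).

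**4. How this applies to each outcome type.**

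- *Counts and costs.* These are compared between arms directly, so a practice effect enters in full. In a simulation of 12 practices of 8 patients (assumed mean count 1, dispersion 1), a negative binomial model without a practice term rejected a true null roughly 5%, 7.5%, 9% and 15% of the time at log-scale practice variances of 0, 0.05, 0.10 and 0.20.
- *Scales.* A practice effect constant over time is present before and after, and so cancels from group x time. What remains is variation between practices in change. The table's rows, including the SF-36 power, hold for the scales only if the ICC is read as that of change.

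**5. If regions are pooled.** A site term only does work in a model with several regions. With three regions of equal weight (assumed) and clustering in one, the variance ratio is (1 + 1 + DE)/3. For DE = 1.35 this is 1.12, and the type I error is about 6.4% instead of 9.2%. For DE = 2.10 it is 1.37, and about 9.4% instead of 17.6%.

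**The case against.** The strongest reply has five parts.

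- *Group x time cancels clustering.* This stands in part. A reader might infer that every Canterbury standard error is too small by the full design effect. For the scales the documents do not support that, because a stable practice effect drops out. The reply does not reach the count and cost models.
- *Practices may contribute very few patients.* This stands as a limit on size. Canterbury enrols COPD patients on home long-term oxygen, of whom the Recruitment section counts about 250 at any one time. One to three per practice cannot be excluded, and the effect would then be slight unless the ICC is high.
- *The model may pool regions.* The site term suggests so, and pooling dilutes the inflation. But the protocol also calls each region a stand-alone trial, and pooling does not remove the problem.
- *The separate planning document may allow for clustering.* It is not available here, so the absence of a design effect is an inference from the identical 120, not an established fact. Such an allowance would in any case leave the stated models unchanged.
- *This is a pilot.* The protocol says it is not powered to confirm effectiveness for most outcomes. That softens the power point, but the protocol still claims 90% power and still tests at p ≤ 0.05.

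A reader might also infer that the pilot cannot yield a practice-level ICC. That goes too far: each Canterbury patient's practice is confirmed at allocation and the GP is asked about at baseline, so the ICC can be estimated. The protocol only fails to commit to reporting it.

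**Conclusion.** The point holds. The protocol names its random effect and covariates, and followed as written they analyse Canterbury as though patients had been randomised individually. The sample size text shows no allowance for clustering. The direction is clear for counts and costs whenever patients within a practice are positively correlated. For the scales it depends on clustering of change.

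The size cannot be fixed from the documents. The illustrations run from negligible (5.1% type I error, power 89.7%) through moderate (9.2%, about 80%) to large (17.6%, about 61%). The large case is only an assumed upper end; nothing in the protocol points to 12 patients per practice or an ICC of 0.10. All these figures assume equal practice sizes and a stand-alone Canterbury comparison, and the power figures also assume that 120 gives exactly 90% without clustering.

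**What to change.** In every analysis that includes Canterbury patients, treat practice as the randomised unit:

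- *Counts and costs:* add a practice random effect, or use standard errors clustered on practice.
- *Scales:* use a practice random effect that also allows practice-by-time variation, since an intercept alone cancels from the tested contrast. If that variance cannot be estimated well, analyse change with standard errors clustered on practice.
- *Few practices:* apply a small-sample correction for the number of clusters.
- *Sample size:* restate Canterbury's power with an assumed ICC and practice size, labelled as assumptions, or state where the existing calculation already allows for them.
- *Reporting:* commit to reporting the estimated practice-level ICC for the follow-up trial.

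This changes wording and analysis code only and needs no new data, because practice is already recorded. The cost is somewhat wider intervals and a lower stated power for Canterbury.

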# Study Design

ASSET will be conducted as:

- **Three separate randomised controlled trials** in Auckland, Counties Manukau and Canterbury (there will be no control group in Tairawhiti)
- Within each of the active intervention arms, including Tairawhiti, there will be an **action research process to optimise the telecare system intervention.**
- Within each control arm there will be a **process of mapping real usual care.**

Each region will stand alone as a discrete trial though with some shared outcomes. Standard criteria and measures will apply across all trials.

The telecare equipment will be available to all four health services for 12 months, with equipment loaned to any one patient for up to three months.

Participants will be assessed at baseline with follow up at three (immediately post intervention) and six months (three months post intervention).

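### The age, gender and site adjustment in the scale models is close to inert, because the effect is read from the group-by-time interaction

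*Protocol*

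**What the plan says.** The Analysis section of the protocol fixes both the model and the quantity read from it. Continuous outcomes are analysed with "mixed effects models that included site as a fixed effect, patient as a random effect and adjusted for age and gender". It then states: "The main outcome for the psychometric scales will be assessed from the interaction between intervention group and time". The Study Design section sets three assessments: baseline, three months and six months. No covariate-by-time term is mentioned.

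Three other statements bear on the point.

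- The randomisation section records that "initially we intended to randomise with stratification by age / gender / distance from hospital / ethnicity", and that this was dropped deliberately. It adds: "From this pilot data we will be better informed as to whether stratification will be necessary in a follow up trial". The Analysis section repeats that the findings will inform that choice.
- The negative binomial models for hospital use and costs are "adjusted for patient age, gender, ethnicity, and site as a factor variable". The Analysis section also plans further work: "Exploratory analysis will assess the influence and associations of explanatory and potentially confounding variables".
- Under Statistical Issues the protocol expects that "about 20% will drop out", with deaths of about 20% per year in COPD and heart failure. Missing data will not be imputed.

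**The concern.** Age at entry, gender and site do not vary within a patient. Entered as main effects beside a patient random effect, they explain differences in level between patients. The group-by-time interaction compares changes within patients. The adjustment therefore acts on a part of the model that is not reported, while the report would describe the scale effects as adjusted for age and gender.

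Two things are at stake. First, allocation is unstratified and each trial is small: Appendix 8 plans 8 recruits a month for 12 months, which is 96 patients or 48 per arm. A chance difference between arms in a covariate that affects recovery would pass uncorrected into the scale effects. Second, the pilot is meant to show whether later trials need stratification. If that is judged by whether adjustment moves the scale effects, this model points towards no because of its form, whatever the data show.

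**Working it through.** No figure in the protocol states the effect of the adjustment, so there is none to reproduce. The sample-size text gives no SD. Reading 120 as per region (60 per arm), the implied two-sided SD is 10 / [(1.960 + 1.282) × √(2/60)] = 16.9. It is used below only to set a scale.

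**1. Algebra.** Write the planned model for patient i at visit t as

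y(i,t) = level + b·age + c·gender + site + u(i) + visit(t) + d·arm + e(t)·arm + error.

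Subtracting baseline gives

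y(i,t) − y(i,0) = visit(t) − visit(0) + e(t)·arm + error difference.

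The age, gender, site and patient terms have gone. With complete visits, the estimate of e(t) is the difference in mean change between arms, whether or not those terms are fitted. If age also alters the course, with slope s(t) on change, the estimate is off by s(t) × (difference in mean age between arms), and an age main effect does not touch that.

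**2. Complete visits, simulated.** Assumed: 120 patients, three visits, patient SD 14, residual SD 10, true effect 3, level falling 5 points per SD of age; 60 data sets. The expected SE is √(2 × 10² × 2/60) = 2.58. Adding age, sex and site main effects changed the month-3 interaction by 0.00000 and left the SE at 2.582. The group main effect, which is not the reported quantity, moved by 0.91 points on average.

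**3. Expected losses.** Six-month deaths of about 10% with 20% drop-out give 1 − 0.80 × 0.90 = 28%, or 30% if simply added.

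| Simulation | Shift from main effects | Shift from covariate-by-visit terms |
| --- | --- | --- |
| 30% attrition, month 3 | 0.12 to 0.17 mean absolute (largest 0.46 to 0.71) | 0.19 to 0.53 mean absolute (age only) |
| 28% loss, month 6, age imbalance 0.3 SD | 0.32 mean absolute (signed mean −0.03) | about 1.6 |

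In the first row, main effects moved the SE only from 2.781 to 2.778, or from 2.902 to 2.898 with an age-by-time effect present. In the second row the signed mean near zero shows that the shift is noise, not correction.

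**4. What the change contrast already removes.** A 0.5 SD age imbalance was forced (60 per arm, true effect 3, 200 data sets).

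- Age affects level only: the planned interaction averaged 3.29 (Monte Carlo SE about 0.18), compatible with 3. An unadjusted follow-up-only comparison averaged 0.91.
- Age also lowers the course by an assumed 3 points per SD per visit: the expected error at month 3 is 0.5 × (−3) = −1.5. The planned interaction averaged 1.44; with age-by-time added it averaged 3.01.

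**5. Size of what remains.** At 48 per arm the standardised imbalance in one covariate has SD √(2/48) = 0.204, so an imbalance of at least 0.3 SD has probability 0.14 (0.10 at 60 per arm). With an assumed slope of 5 points of change per SD, a 0.3 SD imbalance gives 0.3 × 5 = 1.5 points. With SD 16.9 and an assumed visit correlation of 0.5, the SE of the change contrast is 16.9 × √(2/48) = 3.45, so 1.5 points is 0.43 of an SE.

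**6. Precision.** Where a real age-by-time effect was assumed, covariate-by-visit terms lowered the SE from 2.694 to 2.596 (3.6%) in one set and from 3.556 to 3.514 (1.2%) in another. Where there was none, age-by-visit raised it from 2.582 to 2.596 (0.5%).

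**The case against.** The strongest reply is that little is lost. The terms are redundant because the change contrast already removes level imbalance. Under individual randomisation, an interaction without covariates is unbiased over allocations, and its standard error already allows for chance imbalance. The gain in precision is under 4%. The study is a pilot, not powered for most outcomes, and exploratory analysis of confounders is planned. All of this stands and limits the point to a cheap improvement.

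It can also be said that the functional form of an adjustment is commonly left to an analysis plan, which is not shown here. That carries less weight: the protocol fixes both the model and the estimand, and on the natural reading of adjustment the two together make the stated terms ineffective.

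A reader might infer more than the documents support:

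- **That the terms can never change the result.** This is exact only with complete visits. With the expected losses the terms move the estimate slightly, and they help if missingness depends on age or gender.
- **That dropping stratification leaves no other protection.** The protocol does not offer covariate adjustment as the replacement for stratification. Randomisation, the change contrast and the exploratory analysis remain, and the count models adjust in a form that does act on the group comparison.
- **That site imbalance distorts the results.** The protocol makes each region a stand-alone trial, where site is constant. A site effect arises only if regions are pooled, and any figure for it needs assumed recovery rates and arm splits.
- **That leaving ethnicity out of the scale models is an error.** It differs from the count models, but whether to add it is a choice.

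**Conclusion.** The point holds as a specification weakness. On the main-effects reading, adjustment for age, gender and site leaves the group-by-time effect exactly unchanged with complete visits and nearly unchanged under the protocol's own attrition, so the scale effects would be called adjusted when in essence they are not. The exact zero rests on no assumed value.

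The exposure is narrow: chance imbalance in covariates that alter the course over time, and a standard error about 1% to 4% larger than it need be. The 1.5-point illustration rests on an assumed imbalance and slope, neither from the protocol, and is under half a standard error. The statement that the comparison is unbiased on average covers the individually randomised regions, Auckland and Counties Manukau; Canterbury allocates by practice. The adjustment as written is also a poor guide to whether later trials should stratify.

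**What to change.** In the Analysis section, state that age and gender enter the scale models with their interaction with visit, for example `c.age##i.visit i.gender##i.visit` in Stata. Equivalently, state that the arm difference in change is estimated at each follow-up visit with these covariates acting on that visit. Add site-by-visit only if regions are pooled. Adding ethnicity with its visit interaction, to match the count models, is optional; its cost grows with the number of categories.

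The cost is one sentence and one line of code. Age and gender over two follow-up visits add four interaction terms (2 × 2). No new data are needed: both are already in the baseline data of Appendix 1.
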